##### Oncologist questionnaires

In order to collect information on advance care planning and the making of end-of-life decisions (ELDs), the oncologist will be asked to fill out a validated Dutch questionnaire that has been used many times before in nationwide ELD-incidence studies in Flanders, Belgium. In accordance with previous studies, three main categories of ELDs will be considered: the withholding or withdrawal of potentially life-prolonging treatments (non-treatment decisions), the intensified alleviation of symptoms with a possible life-shortening effect and the administration or supply of drugs with the intention of shortening the patient’s life (physician-assisted death) [27, 28].

Data on outcomes related to treatment characteristics will be collected from the medical records of the patient, including survival time, intensity of chemotherapy, hospital admissions and frequency of contact with a psychologist/dietician/other health care professional. According to the definitions of Temel et al., patients will be classified as having had aggressive care if they meet one of the following criteria: 1) chemotherapy within 14 days of death, 2) no palliative care involvement in the last three months of life, or 3) admission to a palliative care unit three days or less before death [4].

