
In Belgium standard oncology care in the hospital is organised on a multidisciplinary model. At the medical level, specialists from different disciplines work closely with each other in diagnosing and treating the patient. At a paramedical level, many resources are devoted to ensuring psychosocial support for cancer patients; every hospital in Belgium with an oncology department has a psychosocial team available for patients and their family carers, consisting of a psychologist, a social worker, a dietician and a nurse specialist. Consultations with the professional caregivers of these teams are free of charge and a first consultation is often organized at the start of treatment. Because of government funding, all hospitals in Flanders, Belgium have a small palliative care team (palliative care nurse 0.5 FTE, palliative care physician 0.5 FTE and palliative care psychologist 0.5 FTE for every 500 hospital beds) available for patients who no longer receive curative treatment or care at the hospital. Palliative care teams are not structurally embedded into the psychosocial team for cancer patients but consultations with them are also free of charge. Patients are mostly seen by a palliative care nurse from the palliative care team [13]. Despite the availability and financial accessibility of palliative care teams, palliative care professionals are only involved in the care of about 60 % of patients with advanced cancer and they are often involved late in the disease trajectory of these patients [14], hence a programme which focuses on systematically providing palliative care early in the disease trajectory of advanced cancer patients is an innovative approach for cancer patients in Flanders, Belgium.

The systematic early integration of palliative care (IPaC) study is the first RCT study on early palliative care for advanced cancer patients to be conducted in the Belgian health care setting. The overall aim of the present paper is to describe the IPaC study protocol.

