#### Palliative care consultation

The intervention consists of systematic consultations with the palliative care nurses of the palliative care team of the Ghent University Hospital shortly after diagnosis of advanced cancer or of the progression of the disease. The palliative care team of the Ghent University Hospital consists of three palliative care nurses (2.5FTE), a palliative care psychologist (0.5FTE) and a palliative care physician (0.5FTE). This systematic early integration of palliative care will be in contrast to standard oncology care, where referral to palliative care is only at the request of physicians, nurses or patients and mostly occurs late in the disease trajectory. The participant receiving systematic early palliative care will meet with the palliative care nurses at least once a month and more if needed or requested by the patient. The palliative care physician will support and advise the palliative care nurses and will have at least one consultation every three months with the participant. All consultations will take place at a time when the patient is at the hospital for diagnostic or therapeutic reasons. The content of the palliative care consultations will be based on the holistic approach of palliative care and will focus on illness understanding and illness perception, symptom burden, psychological coping, spiritual coping and medical decision making by the patient and his or her informal caregiver.

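### The aggressive-care composite counts lack of palliative care as aggressive care, so the comparison between arms is partly circular and tends to favour the intervention

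*Protocol article*

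**What the plan says.** The section *Oncologist questionnaires* lists treatment characteristics to be taken from the medical record and then defines a binary outcome: "patients will be classified as having had aggressive care if they meet one of the following criteria". The criteria are:

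1. "chemotherapy within 14 days of death"
2. "no palliative care involvement in the last three months of life"
3. "admission to a palliative care unit three days or less before death"

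The definition is attributed to the earlier early-palliative-care trial in metastatic non-small-cell lung cancer.

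*Palliative care consultation* describes the randomised treatment. The intervention participant "will meet with the palliative care nurses at least once a month and more if needed or requested by the patient", and the palliative care physician sees the participant at least once every three months. The same section limits the setting: "All consultations will take place at a time when the patient is at the hospital for diagnostic or therapeutic reasons".

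Controls are not barred from palliative care. Under *Standard care* and *Ethical considerations* they can have it on request or referral, and that referral is said to come mostly late. For usual care, *Background* states that "palliative care professionals are only involved in the care of about 60 % of patients with advanced cancer".

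*Statistical analysis and sample size calculation* plans Fisher's exact and chi-square tests, among others, to compare study outcomes between groups. Nothing exempts the aggressive-care classification or separates its parts.

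**The concern.** Criterion 2 is close to being the absence of the randomised treatment. An intervention patient seen on schedule through the last three months of life cannot meet it, since both the monthly nurse contact and the three-monthly physician contact satisfy it. A control patient meets it whenever no referral takes place in that window. The eligibility rules in *Study participants* add to this. A patient with a palliative care consultation in the six months before inclusion is excluded, so a control who dies within three months of inclusion meets criterion 2 unless newly referred.

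Because one criterion is enough, a difference in criterion 2 carries into the composite. The trial could then find less aggressive care in the intervention arm when only the delivery of consultations differed, with chemotherapy near death and late unit admission unchanged.

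**Working it through.** **The plan's own figure.** The article gives no figure for aggressive care. Its only computed figure is the sample size for quality of life. With a difference of 12, SD 23.0, 80% power and an assumed two-sided alpha of 0.05, the normal formula gives 2 × (1.96 + 0.842)² × 23² / 12² = 57.7, so 58 per arm. The t-test version gives 58.6, so 59 per arm and 118 in total. Then 118 / 0.65 = 181.5, so 182. The figure reproduces, and the composite plays no part in it.

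**Inputs for the composite**

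- c = share of decedents with no palliative care contact in the last three months (criterion 2). *Background* gives about 60% involvement in general, so 40% is used as a high value for controls. It is an assumption, because the 60% is neither a last-three-months rate nor a rate in trial controls. Lower control values of 20% and 10% are also shown. For the intervention arm, 0%, 5% and 10% are assumed.
- q = share meeting criterion 1 or 3. It is not given. It is assumed to be 20-30%, equal in both arms (no true effect) and independent of criterion 2.
- Deaths per arm are not given; 50 is assumed. The test is Fisher's exact, two-sided 0.05, with the rejection probability summed over the two binomial distributions.

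**Formula.** P(composite) = 1 − (1 − q)(1 − c), so the built-in difference is (1 − q) × (c_control − c_intervention).

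- c = 40% vs 0%, q = 20%: 1 − 0.8 × 0.6 = 52% vs 20%, difference 32 points.
- c = 40% vs 0%, q = 30%: 1 − 0.7 × 0.6 = 58% vs 30%, difference 28 points.
- c = 10% vs 0%, q = 20%: 1 − 0.8 × 0.9 = 28% vs 20%, difference 8 points.
- c = 10% vs 0%, q = 30%: 1 − 0.7 × 0.9 = 37% vs 30%, difference 7 points.

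| c, control vs intervention | Built-in difference, q = 30% to 20% | Fisher significant, 50 deaths per arm |
|---|---|---|
| 40% vs 0% | 28 to 32 points | 77 to 90% |
| 40% vs 10% | 21 to 24 points | 50 to 63% |
| 20% vs 5% | 10.5 to 12 points | 14 to 20% |
| 10% vs 0% | 7 to 8 points | 8 to 11% |

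With 30 deaths per arm, the first row falls to 50-66%. An unpooled z-test at 50 deaths gives 84-94% for the first row, but the article names Fisher's exact and chi-square tests.

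**With criterion 2 removed** and q equal in both arms, the expected difference is 0 and the rejection rate is no more than the nominal 5%.

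**Dependence between criteria.** In general, the built-in difference is the between-arm difference in the share who meet criterion 2 and neither of the others. Take c = 40% vs 0%. If criterion 2 never overlaps the others, the difference is the full 40 points. If the overlap in controls is as large as possible, it is 40 − 20 = 20 points at q = 20% and 40 − 30 = 10 points at q = 30%. For c = 10% vs 0% the same bounds are 10 and 0 points.

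**The case against.** A reader might infer that the intervention determines this outcome and that a large difference is guaranteed. The documents do not support that:

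- Controls may receive palliative care. Referral that comes late may still fall inside the three-month window.
- The *Discussion* acknowledges crossover to controls, and that consenting patients may be more open to end-of-life discussions. Both could reduce the number of controls without contact.
- Intervention contacts occur only when the patient is at the hospital, and patients may withdraw, so some intervention decedents may also lack contact.
- Criteria 1 and 3 classify patients in either arm.
- The 60% figure describes involvement in general.

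Independence is also doubtful. A patient admitted to a palliative care unit would ordinarily have had palliative care involvement, so criteria 2 and 3 hardly overlap, which enlarges the built-in gap. Late chemotherapy in unreferred patients would make criteria 1 and 2 overlap, which shrinks it. Criterion 3 is itself partly a measure of access. The nurses' referring role could raise it in the intervention arm and work against the built-in difference.

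On weight, aggressive care is not the primary outcome and *Study objectives* does not name it. No sample size rests on it. Chemotherapy intensity and hospital admissions are collected separately, and the definition was taken from a cited trial, presumably for comparability.

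All of this stands as a limit on size, certainty and importance. It does not remove the overlap between criterion 2 and the assigned treatment, and borrowing the definition does not remove it either.

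**Conclusion.** The point holds as a partial circularity in a non-primary outcome. Criterion 2 largely measures receipt of the randomised treatment. Whenever fewer intervention than control decedents lack contact, the composite therefore tends to favour the intervention without any change in late chemotherapy or late unit admission.

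How far it does so cannot be read from the documents. The calculated range, from a difference that Fisher's test would rarely detect to one that it would usually detect, rests on assumed values for both contact rates, for q, for independence of the criteria and for the number of deaths. The upper end also treats the general 60% involvement figure as if it applied to trial controls in their last three months. This is a correction worth making to one outcome definition. It does not threaten the trial's main conclusion on quality of life.

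**What to change.** - Report the three criteria separately by arm.
- Base any test of treatment intensity near death on criterion 1 and criterion 3, each shown separately. Read criterion 3 with care, because the intervention's referring role may also affect it.
- Report palliative care involvement in the last three months as a process and contamination measure. That would also inform the crossover concern raised in the *Discussion*.
- If the three-part composite is kept for comparability with the cited trial, label it descriptive and do not test it.

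The cost is about one sentence in the outcome definition. The components are already part of the medical-record data collection. The downside is less direct comparability with the cited trial's composite.

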#### Statistical analysis and sample size calculation

To compare baseline characteristics and study outcomes for patients between groups, Fisher’s exact tests, chi-square tests and the independent-samples t-test or the non-parametric equivalent Mann–Whitney *U* will be used. The effect of early palliative care on the primary outcome quality of life will be assessed by multivariate regression analyses adjusting for baseline scores. Survival analysis, i.e. Kaplan-Meier and a Cox proportional hazards model, will be used to examine the effect of systematic early integration of palliative care on the secondary outcome survival from the time of inclusion adjusting for demographic and clinical baseline characteristics. With regard to missing data, we will use the conservative approach of carrying the last observation forward for all missing data.

To detect a significant and meaningful difference in the change of the EORTC QLQ-C30 from baseline to 12 weeks, 118 patients are needed. With the proposed sample size of 59 for the two groups, the study will have a power of 80 % to yield a statistically significant result. This computation assumes a mean score difference of 12 and the common within-group standard deviation is 23.0. A difference of 10 points on the multi-items scales from 0 to 100 is considered meaningful (50;51). On the basis of the study on early palliative care in advanced lung cancer patients, it can be expected that approximately 80 % of the study participants will still be alive at 12 weeks after inclusion and drop-out for reasons other than death will amount to 15 % [4]. In other words, an overall drop-out rate of 35 % is to be expected, accounting for the planned inclusion of a total of 182 patients in the study.

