### Outcome measures

#### Study objectives

The primary objective of this study is to assess the impact of this intervention’s systematic early integration of palliative care on the patient’s quality of life. The secondary objectives are (1) to assess the impact on the patient’s median survival time, mood and illness understanding, (2) the impact on informal caregivers’ quality of life, mood, illness understanding and satisfaction with care during treatment and after the death of the patient and (3) to examine whether systematic early integration of palliative care, alongside hospital treatment and treatment characteristics, influences advance care planning and end-of-life decision-making.

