##### Patient and informal caregiver questionnaires

Quality of life of the patient will be measured with the use of the European Organisation for Research and Treatment of Cancer Quality of Life Questionnaire (EORTC QLQ C30) and the McGill Quality of Life Questionnaire (MQOL) [17–19]. The MQOL has been selected because it addresses the existential aspects of quality of life as well as the physical, emotional and social aspects of quality of life. A recent review qualified both its content and construct validity as high [20]. The mood of the patient will be measured by two instruments: the Hospital Anxiety and Depression Scale (HADS) and the Patient Health Questionnaire 9 (PHQ-9) [21–24]. Illness-understanding will be measured by a forward-backward translation of the questionnaire developed by the researchers of the previously mentioned study of palliative care for patients with metastatic non-small-cell lung cancer [4]. Data on mood, quality of life, illness understanding and satisfaction with care of the informal caregivers will be obtained by self-assessment instruments: HADS, PHQ-9, the Short Form-36 Health Survey (SF-36) a questionnaire for illness understanding and by the FAMCARE respectively [25]. A forward-backward translated and tested version of the FAMCARE will evaluate the satisfaction with care of the informal caregivers [26].

The surveys filled out by patients and informal caregivers, their frequency and the timing of completion are detailed in Table 3. The patient will complete the baseline questionnaires before randomization and the follow-up questionnaires with regard to quality of life, mood and illness-understanding firstly after 12 weeks and thereafter every six weeks. Change from baseline to 12 weeks after inclusion is chosen because approximately 80 % of patients are expected to be alive at 12 weeks after inclusion [4]. The informal caregivers will complete the baseline questionnaire before randomization and the follow-up questionnaires firstly after 12 weeks and then every six weeks. If the patient dies the informal caregiver is asked to fill out the questionnaire once more 12 weeks after the death.

**Table 3 Tab3:** Types of patient and informal caregiver questionnaires and frequency and timing of completion

	Week					
	Baseline	12	18	24	…	12 weeks after patient’s death
PATIENT FORMS						
EORTC QLQ C30 and MQOL	X	X	X	X	X	
PHQ-9 and HADS	X	X	X	X	X	
Illness-understanding Questionnaire	X	X	X	X	X	
INFORMAL CAREGIVERS FORMS						

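### Patient mood scores (HADS, PHQ-9) are planned for unadjusted two-group tests although both are measured before randomization, which gives up precision

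*Protocol article*

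**What the plan says.** All four relevant statements are in the Protocol article.

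- **General rule** (Statistical analysis and sample size calculation): the article lists Fisher's exact and chi-square tests, then "the independent-samples t-test or the non-parametric equivalent Mann–Whitney", for patient outcomes and baseline characteristics alike. No covariates are mentioned.
- **First adjusted analysis** (same section): "the primary outcome quality of life will be assessed by multivariate regression analyses adjusting for baseline scores".
- **Second adjusted analysis** (same section): a Cox model for "the secondary outcome survival from the time of inclusion adjusting for demographic and clinical baseline characteristics".
- **Mood**: Study objectives lists as secondary "to assess the impact on the patient’s median survival time, mood and illness understanding". Under Patient and informal caregiver questionnaires, "The mood of the patient will be measured by two instruments", namely HADS and PHQ-9. The same section says that "The patient will complete the baseline questionnaires before randomization", and Table 3 schedules both mood scales at baseline, at week 12 and every six weeks after that.

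**The concern.** Two patient outcomes are given adjusted models, and mood is neither of them. On the text, HADS and PHQ-9 therefore fall under the general sentence and are tested without their baseline values, although those values are collected on the same forms and schedule as the quality-of-life scores that are to be adjusted.

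The sample size is set for the QLQ-C30 only, so nothing guarantees adequate power for mood. A method that discards a prognostic baseline score makes a moderate mood effect easier to miss. A two-sample test also cannot use department, the factor on which randomization is stratified.

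**Working it through.** **Step 1: the plan's own figure.** Inputs from the statistical section: mean difference 12, SD 23.0, power 80%, 59 per arm, 35% drop-out. Two-sided 5% significance is assumed, as the article does not state it. The standardised effect is 12/23.0 = 0.52. The two-sample t-test needs 58.6, so 59 per arm, and power at 59 is 80.2%. Inflation: 118/(1 − 0.35) = 181.5, so 182. The plan's figures reproduce. They concern the primary outcome and this point does not change them; 59 per arm is used below only as a convenient size.

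**Step 2: variance formulas.** Let rho be the correlation between baseline and follow-up score, with equal variance at both times. Variance of the treatment effect relative to a t-test on follow-up scores:

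- t-test on change scores: 2(1 − rho)
- regression on arm and baseline score (ANCOVA): 1 − rho²
- hence ANCOVA relative to change scores: (1 − rho²)/[2(1 − rho)] = (1 + rho)/2

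Both ANCOVA ratios are below 1 for any rho strictly between 0 and 1, so it does not matter for the direction of the result which score the unadjusted test would use.

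**Step 3: numbers.** The article gives no rho; 0.3 to 0.7 is assumed.

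| rho | ANCOVA vs follow-up score, 1 − rho² | ANCOVA vs change score, (1 + rho)/2 |
|---|---|---|
| 0.3 | 0.91 (9% lower) | 0.65 (35% lower) |
| 0.5 | 0.75 (25% lower) | 0.75 (25% lower) |
| 0.7 | 0.51 (49% lower) | 0.85 (15% lower) |

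**Step 4: power.** Two-sided 5% t-test, 59 per arm, assumed standardised effect d = 0.45. The effective d is 0.45 for follow-up scores, 0.45/√[2(1 − rho)] for change scores and 0.45/√(1 − rho²) for ANCOVA.

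| rho | Follow-up score | Change score | ANCOVA |
|---|---|---|---|
| 0.3 | 68% | 54% (d 0.38) | 72% (d 0.47) |
| 0.5 | 68% | 68% (d 0.45) | 80% (d 0.52) |
| 0.7 | 68% | 88% (d 0.58) | 92% (d 0.63) |

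At the plan's own standardised effect of 0.52 instead of 0.45, power on follow-up scores is 80%, and ANCOVA gives 84%, 90% and 98% at rho 0.3, 0.5 and 0.7.

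**The case against.** The strongest reply is that the general sentence is a list of tests and not an exclusive plan for mood. It names neither HADS nor PHQ-9, and it covers study outcomes as a whole, including quality of life and survival, which then receive adjusted models anyway. A separate analysis plan could add one for mood. This has weight, but the article does say which outcomes are adjusted, and mood is left with the unadjusted tests. The point is about what is stated.

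Other objections limit the point:

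- **Efficiency, not validity.** A reader might infer that the mood results would be biased or distorted. The documents do not support that. Allocation is randomized 1:1, the unadjusted tests are valid, and chance baseline imbalance is already reflected in their standard error.
- **The comparator is not fixed.** The article words its 12-week quality-of-life endpoint as change from baseline. If mood is also tested on change scores, the baseline is already partly used, and at rho 0.7 the gain is only 88% to 92%.
- **The number analysed may exceed 59 per arm.** Last observation carried forward is planned for all missing data, so up to 182/2 = 91 per arm could be analysed. At 91, d = 0.45 and rho 0.5, power is 86% unadjusted and 94% adjusted. The variance ratios do not change.
- **MQOL.** A reader might infer that it too is compared unadjusted. The article lists it as a quality-of-life measure beside QLQ-C30, so it may already be under the adjusted model, although the Discussion names QLQ-C30 as the primary measure. This is an ambiguity to clear up, not an error.
- **Caregiver scales.** A reader might extend the point to them because they also have baselines. The sentence is limited to patients, and the article assigns no test to caregiver outcomes.
- **Mann–Whitney.** It might be said to give no effect estimate. It can be accompanied by a Hodges–Lehmann shift estimate with a confidence interval.

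**Conclusion.** The point holds for patient HADS and PHQ-9: as written, they are compared without baseline adjustment although a pre-randomization score exists for each. The consequence is avoidable loss of precision in a secondary objective: 9% to 49% of the variance against follow-up scores, or 35% to 15% against change scores, for rho from 0.3 to 0.7. The direction does not depend on which score is tested. The size does, and it rests on an assumed rho; the power illustration also rests on an assumed d of 0.45. At the weak end (rho 0.3, follow-up scores) the gain is small, 68% to 72%.

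It does not touch the primary analysis, the sample size, survival (which has an adjusted Cox model) or outcomes without a baseline. It is a minor to moderate improvement that is available at almost no cost.

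**What to change.** State that patient HADS and PHQ-9 will be analysed by the baseline-adjusted regression already planned for quality of life: follow-up score on arm and the patient's own baseline score. Add the stratification factor, department, as a covariate; the stated primary model mentions baseline scores only, so this is an addition. Report the adjusted difference with its 95% confidence interval.

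Confirm in one sentence whether MQOL is under the same model. Applying the model to caregiver scales that have a baseline (SF-36, HADS, PHQ-9, FAMCARE) is a sensible extension.

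Keep the t-test or Mann–Whitney and the chi-square or Fisher tests for outcomes without a baseline value. Among these are the binary end-of-life and aggressive-care outcomes, for which chi-square and Fisher are the only tests the article states.

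The cost is a few sentences of statistical text. No extra data are needed, since Table 3 already schedules all these scales at baseline.

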## Methods

### Study design

This is a phase III randomized controlled trial (RCT) in a hospital setting with advanced cancer patients receiving systematic early integration of palliative care with standard oncology care versus advanced cancer patients receiving standard oncology care alone. Study participants will be randomized in a 1:1 fashion to the intervention arm or standard care arm. Patients will be recruited from the Digestive Oncology, Thoracic Oncology and Medical Oncology departments of the Ghent University Hospital, the second largest hospital in Belgium. These departments have been selected for the trial because almost all cancer patients in the Ghent University Hospital are treated in these departments. Stratification will take place for the treating oncology department (Digestive Oncology, Thoracic Oncology and Medical Oncology) in order to prevent imbalances between groups in factors related to possible differences in standard care [15].

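### Randomisation is stratified by oncology department, but the primary quality-of-life model names only baseline scores as adjustment: a modest, conservative loss of precision that costs nothing to remove

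*Protocol article*

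**What the plan says.** Design (Protocol article, Study design). Allocation is 1:1, and "Stratification will take place for the treating oncology department", with digestive, thoracic and medical oncology as the three levels. The reason given is "in order to prevent imbalances between groups in factors related to possible differences in standard care".

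Primary analysis (Statistical analysis and sample size calculation). The effect on quality of life "will be assessed by multivariate regression analyses adjusting for baseline scores". Department does not appear in that sentence, and no other sentence of the article carries it into an analysis.

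Survival analysis (same section). The Kaplan-Meier and Cox analysis concerns "survival from the time of inclusion adjusting for demographic and clinical baseline characteristics". This wider adjustment is stated for survival only.

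Sample size (same section). "This computation assumes a mean score difference of 12 and the common within-group standard deviation is 23.0"; the result is 59 evaluable patients per arm, 118 in total, and 182 to be included after an expected loss of 35%.

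**The concern.** Stratified allocation makes the arms alike on department. The treatment estimate therefore does not vary from trial to trial because of department mix. A regression that leaves department out does not know this. It puts any between-department variation into the residual and reports a standard error larger than the real spread of the estimate. The confidence interval is then too wide, the test rejects a true null less often than its nominal level, and some power is given away.

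The article's reason for stratifying treats department as possibly related to outcome. The factor thought important enough to control in the design is thus absent from the stated primary model. The power calculation meets 80% with little to spare, so precision that can be had for nothing is worth taking.

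**Working it through.** **Inputs from the article.** Difference 12 points; standard deviation 23.0; 59 per arm; 80% power; 35% overall loss; three departments; 1:1 allocation.

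**Assumptions.** Two-sided alpha of 0.05: the article does not state alpha, but this value reproduces its sample size, whereas one-sided 0.05 would give 46 per arm. R² is the share of outcome variance that department explains beyond the baseline score. The article gives no figure for it, so a range from 0 to 20% is used. The 23.0 is taken as the standard deviation before department is accounted for.

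**Step 1: reproduce the plan's figures.**
- Normal approximation: n per arm = 2 × ((1.960 + 0.842) × 23 / 12)² = 57.7, so 58. Power at 59 per arm is 80.9%.
- Noncentral t: power is 79.6% at 58 and 80.2% at 59 per arm, which gives the stated 59.
- Inclusion: 118 / (1 − 0.35) = 181.5, so 182.

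The stated sample size reproduces and is not in dispute.

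**Step 2: effect of leaving department out, by formula.** The standard error reported without department is 23 × √(2/59) = 4.23. Under stratified allocation the real spread is about 4.23 × √(1 − R²), so the reported value is too large by the factor 1/√(1 − R²). Power with department in the model uses a standard deviation of 23 × √(1 − R²).

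| Assumed R² | Standard error too wide by | Power at 59 per arm, department in model | n per arm for 80% power, department in model |
|---|---|---|---|
| 0% | 0% | 80.9% | 58 |
| 2% | 1.0% | 81.7% | 57 |
| 5% | 2.6% | 82.8% | 55 |
| 10% | 5.4% | 84.8% | 52 |
| 20% | 11.8% | 88.7% | 47 |

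Type I error without department is about 2 × (1 − Φ(1.96/√(1 − R²))). This gives 4.4% at R² = 5%, 3.9% at 10% and 2.8% at 20%.

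**Step 3: check by simulation.** The set-up was 118 patients, three departments equally likely, permuted blocks of four within department, and 8,000 trials per setting. Each trial was analysed by regression on treatment and baseline score, with and without department.

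| Assumed R² | Without: mean reported SE / true SD of estimate | Type I error without | Type I error with | Power without | Power with |
|---|---|---|---|---|---|
| 0% | 4.24 / 4.25 | 5.0% | 5.0% | 79.3% | 79.4% |
| 5% | 4.24 / 4.13 | 4.4% | 4.9% | 79.9% | 81.4% |
| 10% | 4.25 / 4.02 | 3.7% | 4.6% | 81.0% | 83.8% |
| 20% | 4.25 / 3.80 | 2.7% | 4.8% | 82.5% | 87.7% |

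With 8,000 trials the Monte Carlo standard error is about 0.45 percentage points for a power near 80% (√(0.8 × 0.2 / 8,000)) and 0.24 for a type I error near 5%. The 79.9% at R² = 5% is therefore not evidence of power below 80%: at R² = 0, where omitting department can cost nothing, the same simulation gives 79.3%. The mean estimates under the alternative lie between 11.88 and 12.00 and barely differ between the two models, so omission causes no bias.

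The simulation treats the 118 evaluable patients as the blocked set. Losses between randomisation and week 12 would loosen the balance, so type I error without department would sit nearer 5%.

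**The case against.** **The text does not say only.** The article says that the model adjusts for baseline scores; it does not exclude department. It is a condensed account, and a full protocol or analysis plan that is not shown may list department. This stands as a limit: nobody can say that the trial will analyse without department. But the sentence does specify an adjustment for the primary model, the following sentence specifies a wider one for survival, and the only factor the design stratifies on is missing from the first. The point is about what is stated, not about silence.

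**Department may matter little.** The article speaks of possible differences in standard care. Its Standard care section describes one hospital-wide package, in which the only variation tied to diagnosis is the dietician's introductory consultation. The baseline score, already in the model, may absorb most of what department would explain. This stands too, and is why the range starts at zero, where nothing is lost.

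**Stronger readings that the documents do not support.** A reader might infer that ignoring the stratification invalidates the primary test or inflates false positives. The direction is the opposite: the test is conservative and the estimate unbiased. A reader might also infer that the survival analysis loses material power, with the hazard ratio pulled towards 1. That would need a Cox model with no adjustment and departments with very different prognosis. The article already plans to adjust the Cox model for demographic and clinical baseline characteristics, which can reasonably be read to include department. The eligibility criterion of a life expectancy of about one year also makes a wide spread in survival between departments less plausible. No power loss for survival is claimed here.

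**Conclusion.** The point holds for the primary quality-of-life model. As stated, the analysis does not name the factor used to stratify randomisation, and any variance that department explains beyond the baseline score stays in the error term.

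The size is modest: standard errors are 1 to 2.6% too wide if that share is 2 to 5%, 5.4% at 10% and 11.8% at 20%. Simulated power differs by 1.5 points at 5% (81.4 − 79.9), 2.8 points at 10% (83.8 − 81.0) and 5.2 points at 20% (87.7 − 82.5).

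The omission itself is plain in the article. Its consequence rests on an assumed R², on the assumed two-sided 0.05 level and on the simulation's equal departments and blocks of four. Validity and the sample size are not in question. For survival, the point reduces to a request to name department explicitly.

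**What to change.** In the sentence on the primary analysis, state that the regression for quality of life includes treating department (three levels) as a fixed covariate beside the baseline score. In the survival sentence, name department among the baseline characteristics adjusted for, or use it as a stratum. If an analysis plan already does this, align the published wording with it.

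Cost: two degrees of freedom in the primary model, and a change of wording. Department is known for every patient at randomisation, so no new data are needed. The sample size of 182 stays as it is. Fixing the covariate before results are seen also removes a later choice between adjusted and unadjusted estimates.
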